**High risk group**
• Assessing and addressing biopsychosocial risk factors by adopting cognitive behavioural principles to address unhelpful beliefs and behaviours.

**Table 2 T2:** Outcome Measures

	**Domain**	**Measures**	**Time Point (months)**
Primary	Pain and disability	Roland and Morris Disability Questionnaire [38]	0, 4, 12
	Catastrophising	Pain Catastrophising Scale [39]	0, 4, 12
Secondary	Back Pain	Pain intensity: 0–10 numerical rating scales of least & average pain in last 2 wks & current pain	0, 4, 12
		Duration – time since month back pain free [42]	0
	Back-related Leg symptoms	-Leg pain in last week	0, 4, 12
		-Location of leg pain	0, 4, 12
		-Description of pain	0, 4, 12
		-Presence of Numbness/parasthesia	0, 4, 12
	Pain elsewhere	Self complete manikin for bodily pain in last 4 weeks [43]	0, 12
	Global change	Compared to symptoms at baseline	4, 12
	Kinesiophobia	Tampa Scale Kinesiophobia [44]	0, 4, 12
	Illness perceptions	Musculoskeletal Illness Perceptions Questionnaire (MUSC-IPQ(R))^†^	0, 4, 12
	Anxiety/depression	Hospital Anxiety and Depression Scale [45]	0, 4, 12
	Health-related quality of life	Short Form 12 (version 2) [46]	0, 4, 12
	Patient satisfaction	-With current symptoms	0, 4
		-With information received	4
		-With care received	4
		-With back pain knowledge	4
		-Would have same treatment again	4
		-Rating of overall results of care	4
	Patient expectations	-Expectations for LBP status	0
		-Extent to which expectations were met	4
	Employment details	-Current employment status	0, 12
		-Satisfaction with employment	0, 12
		-Current/most recent job title	0, 12
		-Work loss due back problem	0, 12
		-Work loss due to other health problems	0, 4, 12
		-Work performance	0, 12
	Health care	-Primary care consultations	4, 12
	resource use	-Secondary care attendances (NHS and private)	4, 12
		-Additional health care practitioners (NHS and private)	12
		-Prescription and over-the-counter medicines and treatments	12
	Preference-based measure of health-related quality of life	EQ-5D [47]	0, 4, 12

^† ^Instrument in development, Personal Communication, [name].

#### 2) Best Current Care

Patients randomised to the control arm have a 30-minute consultation with an experienced community physiotherapist (not involved in the 'targeted treatment' arm) who is blinded to the results of the STarT Back tool. A management plan is formulated according to normal clinical practice. This may include referral to community physiotherapy if thought necessary.

Patients from both "targeted treatment" and "best current care" arms are advised that they can access their GP for ongoing care in the usual way, and that they should contact their GP if their condition worsens.

### Audit of interventions

At the clinic, both study physiotherapists and community physiotherapists complete case report forms for all patients participating in the trial. This records assessment findings relating to leg pain and documents medication and advice given in clinic. Physiotherapists who deliver the targeted treatment use a standard proforma to record the number of treatment sessions each participant receives, plus details about the treatments delivered at each session. They also receive regular clinical mentoring and supervision sessions with expert members of the STarT Back Trial team who are responsible for training.

### Outcome measures

As the main focus of this trial is secondary prevention of chronic back pain, primary clinical outcomes are changes in the main physical and psychosocial risk factors for chronicity: disability (Roland-Morris Disability Questionnaire (RMDQ)) [38] and pain catastrophising (Pain Catastrophising Scale) [39] (see Table 2). The RMDQ is a recommended disability measure [40] that it is widely used in low back pain studies in Primary Care, and pain catastrophising has been shown to be an important predictor of quality of life.[41]

Secondary outcome measures are described in Table 2. These were selected to fulfil recommendations on outcome data [40], and to capture more fully some aspects of back-related leg pain, psychological measures and quality of life. [42-47] The health economic evaluation will consist of a cost-utility analysis, with utility measured by the EuroQol EQ-5D.[47] To estimate the costs of the study interventions and consider the resource implications for the targeted treatment approach, the 12-month self-report questionnaire will collect resource use data for back pain-specific and generic health care (direct costs) and details of patients work absence due to low back pain (indirect costs). All resources will be costed using UK national averages from freely available sources. [48-51]

### Sample size

The primary outcome measure for this trial is the Roland and Morris Disability Questionnaire (RMDQ) at 12-months. A difference of 2.5 points in RMDQ change scores is considered to be a minimum clinically important difference in the RMDQ.[52] Our sample size calculation is based on two separate hypothesis tests: (i) to test superiority of targeted treatment over best current care for high and medium risk subgroups; (ii) to test non-inferiority of the targeted treatment compared to best current care in the low risk subgroup. For the first hypothesis, a subgroup sample size of 160 patients (107 and 53 per arm based on a 2:1 allocation ratio) would enable detection of a between-group difference of 2.5 RMDQ points given 80–90% power, 5% (two-tailed) significance level, and a conservative standard deviation of 5 points. For the second hypothesis, the targeted treatment will be concluded as being non-inferior to best current care if the lower boundary of the 95% confidence interval for the difference in mean scores for targeted treatment minus best current care (among low-risk participants) is above the threshold of -2.5 points (equivalent to a one-sided test with significance level of 2.5%); 160 patients (107 and 53 per arm) allocated on a 2:1 basis would be able to demonstrate non-inferiority with 80–90% power. Pilot study data estimated that 25%, 50% and 25% of participants would be in the high, medium and low risk subgroups, respectively. These figures were used to extrapolate the total sample size requirement of 640 patients (160 in the high and low risk subgroups and 320 in the middle risk subgroup), which would ensure that we would have at least 80% power for carrying out all three subgroup analyses. 800 participants would need to be recruited to allow for a conservative 20% loss to follow up. Based on a 2:1 random allocation basis, we would therefore expect about 533 and 267 to be recruited to the "targeted treatment" and "best current care" arms, respectively.

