### Data analysis

The primary analysis will be by intention to treat; a per protocol analysis will be performed as a sensitivity analysis. Estimates of treatment effects with 95% confidence intervals ("targeted treatment" minus "best current care") will be calculated. Statistical tests (analysis of covariance (ANCOVA) for numerical outcomes; logistic regression for categorical outcomes) will be performed adjusted for imbalances in the baseline scores. Analyses will be carried out at each time point (4 and 12 months) for primary and secondary outcome measures; the primary endpoint is 12-month follow up. Analyses will be carried out to compare outcomes in patients randomised to "targeted treatment" or "best current care" separately for each of the three subgroups (high, medium and low risk) of patients classified according to the subgrouping tool.

An incremental approach will be used in the economic evaluation. The primary aim is to estimate and compare the societal costs associated with the study interventions and relate this to the difference in the number of quality-adjusted life years (QALYs). QALYs will be calculated by applying area-under-the-curve techniques to the EQ-5D scores at baseline, 4 months and 12 months.[53] Differences in costs and QALYs will be expressed using the incremental cost-per-QALY ratio, with uncertainty addressed using bootstrapping techniques, cost-effectiveness planes and acceptability curves.[54,55] The robustness of the results will be tested by conducting a number of sensitivity analyses; namely, the consideration of alternative perspectives (e.g. adopting an NHS perspective), the effect of incorporating 'generic' health care resource use and the application of multiple imputation techniques to deal with missing data.

An independent data monitoring committee will monitor the trial every 6 months. There will be no interim analyses.

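### As worded, the low-risk non-inferiority rule points the wrong way for a disability score unless the scores compared are improvements, and the protocol never says that they are

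*Protocol article*

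**What the plan says.** All references are to the protocol article.

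- **Endpoint (Sample size):** "The primary outcome measure for this trial is the Roland and Morris Disability Questionnaire (RMDQ) at 12-months". Outcome measures describes the instrument: "The RMDQ is a recommended disability measure".
- **Margin (Sample size):** "A difference of 2.5 points in RMDQ change scores is considered to be a minimum clinically important difference in the RMDQ".
- **Non-inferiority rule (Sample size):** targeted treatment is non-inferior among low-risk participants if the "lower boundary of the 95% confidence interval for the difference in mean scores for targeted treatment minus best current care" "is above the threshold of -2.5 points". The section equates this to a one-sided 2.5% test and states 80–90% power with 107 and 53 patients.
- **Description of the outcomes (Outcome measures):** "primary clinical outcomes are changes in the main physical and psychosocial risk factors for chronicity".
- **Analysis (Data analysis):** effects are estimated as targeted treatment minus best current care, using "analysis of covariance (ANCOVA) for numerical outcomes" with adjustment for baseline. The section does not say whether the dependent variable is the 12-month score or a change, or which direction of change counts as positive.

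**The concern.** A non-inferiority test has to exclude the treatment being worse by the margin or more. On a disability score where higher is worse, with the contrast taken as targeted minus control, being worse lies on the positive side. The limit that matters is then the upper one, and the margin is +2.5. A lower limit above -2.5 shows only that targeted treatment is not better by 2.5 points or more.

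The low-risk comparison is one of the two hypotheses that size the trial. Under Interventions, low-risk patients in the targeted arm have a single 30-minute appointment and no further treatment. Excluding worse disability in these patients is therefore the purpose of the test. If the sign is not fixed in writing, someone applying the sentence literally to RMDQ scores could reach the opposite conclusion, or the direction could be settled after the data are seen.

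**Working it through.** **Inputs (Sample size section):** 107 and 53 patients; margin 2.5; 95% confidence interval; SD 5. The SD is given for the superiority test and is assumed here to carry over. That a higher RMDQ score means more disability is also an assumption, taken from its description as a disability measure.

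**1. Reproduce the stated power.**

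SE = 5 × √(1/107 + 1/53) = 0.840. The interval half-width is 1.96 × 0.840 = 1.65.

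Power at no true difference = Φ(2.5/0.840 − 1.96) = Φ(1.017) = 84.5%. A noncentral t calculation with 158 degrees of freedom gives 84.1%. Both lie within the stated 80–90%. The totals also reproduce: 160/0.25 = 640 and 640/0.8 = 800.

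**2. What the rule accepts.**

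The lower limit exceeds -2.5 when the observed difference exceeds -2.5 + 1.65 = -0.85. There is no ceiling. On RMDQ scores, any observed harm passes, and an observed benefit of 0.85 points or more fails.

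**3. Probability of declaring non-inferiority on RMDQ scores.**

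Let d be the true difference, targeted minus control, with positive meaning targeted is worse.

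- Rule as written: P = Φ((d + 2.5)/0.840 − 1.96)
- Mirrored rule (upper limit below +2.5): P = Φ((2.5 − d)/0.840 − 1.96)

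| True d | As written | Mirrored |
|---|---|---|
| -5 | 0.000 | 1.000 |
| -2.5 | 0.025 | >0.999 |
| -1 | 0.431 | 0.986 |
| 0 | 0.845 | 0.845 |
| +1 | 0.986 | 0.431 |
| +2.5 | >0.999 | 0.025 |
| +5 | 1.000 | 0.000 |

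The two rules have equal probability only at d = 0. That is where the power is computed, so the power statement cannot show which direction was meant.

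**4. The three readings of the scores being compared.**

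| Variable | Harm appears as | Rule as written |
|---|---|---|
| 12-month RMDQ | positive difference | reversed |
| 12 months minus baseline | positive difference | reversed |
| Baseline minus 12 months (improvement) | negative difference | correct |

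**5. Does the analysis model settle it?**

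It does not. With baseline as a covariate, ANCOVA gives the same treatment coefficient for the 12-month score and for follow-up minus baseline. For improvement it gives the same coefficient with the sign reversed. The stated order of subtraction fixes only which arm comes first.

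**The case against.** The best defence is that improvement was intended. The paragraph introduces the 2.5 points as a difference in change scores, the non-inferiority sentence reuses the same 2.5, and Outcome measures calls the primary outcomes changes. A lower limit paired with a negative margin is the usual form when higher is better. On that reading every element of the sentence fits and nothing is wrong with the test. This defence stands as a plausible account of intent. It does not repair the text, because the rule itself speaks of mean scores and no section says which direction of change is positive.

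A second defence is that a condensed article may leave the definition of change to the full protocol or analysis plan. That would answer a complaint about missing detail. Here the article does state the limit, the order of subtraction and the threshold, and on two of the three readings the stated rule is reversed.

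A third is that effect estimates with confidence intervals will be reported, so any harm would be visible. That is true, but the formal conclusion would still rest on the rule.

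A reader might go further and infer that the test is definitely inverted and that the trial would call a harmful result non-inferior. The documents do not support that, because the change-score wording leaves the improvement reading open. Nor does the baseline-adjusted ANCOVA show that raw follow-up scores are meant, for the reason given in step 5 of the working.

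**Conclusion.** The concern holds in conditional form. The rule points the wrong way on 12-month RMDQ scores and on follow-up-minus-baseline change, and the right way on improvement. The protocol article does not say which applies.

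On either of the first two readings, the chance of declaring non-inferiority is above 99.9% instead of 2.5% when targeted treatment is truly 2.5 points worse. It is 2.5% instead of above 99.9% when targeted treatment is truly 2.5 points better. On the third reading no figure changes.

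These figures rest on the normal approximation, on SD 5 applying to the low-risk comparison, and on higher RMDQ meaning more disability. The sample size arithmetic is sound, so this is a fault in the wording of a decision rule and not in a calculation. It still needs correcting, because the conclusion for one of the two hypotheses that size the trial depends on an undefined sign.

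**What to change.** Choose one of two equivalent wordings and use the same convention in Sample size and Data analysis.

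1. **On RMDQ scores:** targeted treatment is non-inferior in the low-risk subgroup if the upper limit of the two-sided 95% confidence interval for the baseline-adjusted mean difference in 12-month RMDQ score (targeted minus best current care; higher = more disability) is below +2.5 points.
2. **On improvement:** define the variable as RMDQ at baseline minus RMDQ at 12 months, so that positive means improvement, and keep the lower limit above -2.5 points for targeted minus best current care.

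The cost is one sentence in Sample size and a matching clause in Data analysis. The 160 low-risk patients, the total of 800 and the stated power (84.5% as recomputed) do not change. The wording should be fixed before any outcome comparison is seen.

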### Interventions

#### 1) Targeted Treatment

All patients randomised to 'targeted treatment' receive an initial 30-minute protocolised intervention with a specially trained study physiotherapist. Patients receive reassurance about the benign nature of their pain, and simple messages of advice around issues such as pain relief, appropriate activity levels and the role of further investigations. The physiotherapist is guided by the results of the patient's STarT Back tool score so that specific concerns can be identified and addressed on an individual basis. To reinforce key messages the 'Back Book' [35] is given, together with an information sheet of local contacts for exercise venues such as swimming pools, gyms and exercise on prescription, and self-help groups. A 15-minute educational video based on The Back Book, called 'Get Back Active' [36] is shown to patients to reinforce key messages. Patients allocated to the 'low risk' group receive no further treatment in addition to this 30 minute clinic appointment.

For patients allocated to receive the medium and high risk subgroup interventions, the study administrator arranges further appointments with specially trained physiotherapists within two weeks of their clinic date. Treatments for the medium and high risk groups were developed after reviewing available literature and guidelines to identify best practice treatment, and are delivered during a target time of six weeks. The focus was to provide secondary prevention of disabling back pain through the provision of treatment targeted at the specific modifiable prognostic indicators identified by the STarT Back tool (see below).

Patients in the 'medium risk' group present with predominantly physical prognostic indicators (disabling back pain, referred leg pain and co-morbid pain), without high levels of psychosocial distress. The 'medium risk' group package of care therefore, targets physical characteristics using a range of physiotherapy techniques delivered over 6, 30-minute sessions. Management includes an assessment and differential diagnosis (particularly for patients with referred leg pain), and treatment designed to reduce disability related to future episodes of low back pain.

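### The subgroup power of at least 80% holds one subgroup at a time, but it and the ANCOVA treat patients of the same physiotherapist as independent although physiotherapists are nested in arm

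*Protocol article*

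**What the plan says.** The protocol article's Sample size section takes the RMDQ at 12 months as the outcome. It says that 160 patients (107 and 53 under 2:1 allocation) "would enable detection of a between-group difference of 2.5 RMDQ points given" 80–90% power, a "5% (two-tailed) significance level" and "a conservative standard deviation of 5 points". The same 160 are said to give 80–90% power for low-risk non-inferiority with a margin of 2.5 points, which is "equivalent to a one-sided test with significance level of 2.5" per cent. Pilot proportions then lead to 160 high-risk, 320 medium-risk and 160 low-risk patients, 640 in all, "which would ensure that we would have at least 80% power for carrying out all three subgroup analyses".

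On delivery, targeted-arm patients "receive an initial 30-minute protocolised intervention with a specially trained study physiotherapist", and those at medium or high risk go on to further physiotherapy sessions. Control patients see an experienced community physiotherapist "not involved in the 'targeted treatment' arm".

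The Data analysis section names ANCOVA adjusted for baseline for numerical outcomes, and compares the arms separately within each risk subgroup. Trial Objectives makes the overall comparison of the two approaches primary and the subgroup comparisons secondary.

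**The concern.** When a small number of physiotherapists treat all the patients, patients of the same physiotherapist tend to have more similar outcomes than patients of different ones. Here the two arms use different physiotherapists. A difference in skill or manner between the two sets therefore cannot be separated from the treatment effect within a physiotherapist, and it enters the treatment contrast as extra variance.

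Two things follow. The effective sample size is smaller than 107 v 53, so power in the 160-patient subgroups is lower than calculated. More seriously, an ANCOVA that treats patients as independent gives a standard error that is too small. Its confidence intervals are then too narrow and its p-values too low. The effect is largest in the overall comparison, the primary objective, because each physiotherapist's caseload is largest there. In the low-risk subgroup a too-narrow interval makes non-inferiority easier to declare.

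**Working it through.** **Inputs from the Sample size section:** difference and margin 2.5; SD 5; two-sided 5% (one-sided 2.5% for non-inferiority); 107 v 53 in the high- and low-risk subgroups. The 320 medium-risk patients split 2:1 as 213 v 107, and the 640 as 427 v 213.

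**Step 1: the plan's own figure.** SE = 5 × √(1/n_T + 1/n_C), with power from the noncentral t distribution.

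- High risk: SE = 5 × √(1/107 + 1/53) = 0.840; power 84.1%.
- Low-risk non-inferiority, assuming a true difference of zero: the same SE; power 84.1%.
- Medium risk: SE = 5 × √(1/213 + 1/107) = 0.592; power 98.8%.

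Each is at least 80%, so the stated figure reproduces per subgroup. It does so with no term for clustering.

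**Step 2: add clustering.** With k physiotherapists in an arm of n patients, the mean caseload is m = n/k, the design effect is 1 + (m − 1) × ICC, and

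variance = 25 × [(1 + (m_T − 1) × ICC)/n_T + (1 + (m_C − 1) × ICC)/n_C].

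**Assumptions, none of them in the document:** 4–15 physiotherapists in the targeted arm and 8–15 in control; one main physiotherapist per patient; equal caseloads; ICC 0.01 or 0.02.

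**Step 3: overall comparison (427 v 213).** The naive SE is 5 × √(1/427 + 1/213) = 0.419. With 4 and 8 physiotherapists the caseloads are 427/4 = 106.75 and 213/8 = 26.6. At ICC 0.01 the design effects are 2.06 and 1.26, and the SE is 0.518. The true type I error of a nominal 5% test is 2 × [1 − Φ(1.96/ratio)].

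| ICC | Physiotherapists (targeted, control) | True SE | Ratio to naive SE | Type I error |
|---|---|---|---|---|
| 0.01 | 15, 15 | 0.456 | 1.09 | 7% |
| 0.01 | 4, 8 | 0.518 | 1.23 | 11% |
| 0.02 | 15, 15 | 0.489 | 1.17 | 9% |
| 0.02 | 4, 8 | 0.600 | 1.43 | 17% |

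**Step 4: high-risk subgroup (107 v 53).** The same formula, with the subgroup shared among the same numbers of physiotherapists:

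| ICC | Physiotherapists (targeted, control) | True SE | Power |
|---|---|---|---|
| 0.01 | 15, 15 | 0.855 | 83% |
| 0.01 | 4, 8 | 0.890 | 80% |
| 0.02 | 15, 15 | 0.871 | 81% |
| 0.02 | 4, 8 | 0.937 | 76% |

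The low-risk figures are the same by symmetry. With a common design effect in both arms, power at 107 v 53 falls to 80% at about 1.12, so these two subgroups have little to spare. Medium risk stays above 90% in all four settings.

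**The case against.** **The stated power is not wrong.** This stands in full. A reader might infer that power for all three analyses is really about 70%, since 0.841 × 0.988 × 0.841 = 0.699. The documents do not support putting that figure in place of the stated one. The Sample size section sizes each test separately, the Data analysis section compares the subgroups separately, and nothing requires all three tests to succeed. The wording only leaves unsaid that the power is per subgroup.

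**Other features work in the opposite direction.** The SD is called conservative, and baseline adjustment raises power. To offset a design effect of 1.12 one needs 1 − r² = 1/1.12 = 0.893, a baseline–outcome correlation of about 0.33, which is also not stated. This stands for power. It does not help the standard error: a smaller residual SD shrinks the naive and the true SE alike, and at a given ICC leaves their ratio unchanged.

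**The size rests on assumptions.** This also stands. Numbers of physiotherapists, caseloads and ICC are not given, and the upper ends come from four targeted-arm physiotherapists with about 107 patients each. A patient may see one physiotherapist at the clinic and another later, and onward physiotherapy for controls is optional, so one main physiotherapist per patient is a simplification. At ICC 0.01 high-risk power remains at about 80% or more.

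**Modelling detail may sit in an analysis plan that is not shown.** That is possible. However, the article lists its sample size inputs, and 107 v 53 reproduces 80–90% with no clustering allowance. It also names the analysis method. The separate physiotherapists are a stated design feature that neither section takes up.

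**Conclusion.** The power statement is correct per subgroup (about 84%, 99% and 84%), conditional on patients being independent within physiotherapist. The design makes that condition doubtful, because the arms have separate physiotherapists. The main consequence is for the analysis. Under the assumed physiotherapist numbers, the overall standard error is too small by a factor of 1.09–1.23 at ICC 0.01 and 1.17–1.43 at ICC 0.02, so a nominal 5% test runs at about 7–11% and 9–17%. The loss of power is secondary: high-risk power of about 80–83% and 76–81%, which baseline adjustment or a smaller SD could make good. These ranges illustrate what is at stake and are not estimates for this trial. If the ICC is zero, the plan's figures stand as they are.

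**What to change.** - **Sample size:** state that the power is for each subgroup taken separately (about 84% high risk, 99% medium risk, 84% low-risk non-inferiority at a true difference of zero) and assumes no clustering by physiotherapist.
- **Data analysis:** add an analysis with a random effect for physiotherapist within arm, or cluster-robust standard errors with a small-sample correction. Report it beside the ANCOVA for the overall and the subgroup comparisons.
- **Audit of interventions:** record a code for the treating physiotherapist on the case report forms that both arms already complete. The article does not say that identity is recorded, so this should be specified.

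The cost is one extra field on a form and one extra model; no more patients are needed. The downside is wider intervals, and an imprecise variance estimate if physiotherapists are few.
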